## **LIST OF ABBREVIATIONS**

|      |                                           |
|------|-------------------------------------------|
| ADE  | Adverse Drug Event                        |
| ADL  | Activities of Daily Living                |
| ADR  | Adverse Drug Reaction                     |
| AE   | Adverse Event/Adverse Experience          |
| CFR  | Code of Federal Regulations               |
| CRF  | Case Report Form                          |
| GCP  | Good Clinical Practice                    |
| ICF  | Informed Consent Form                     |
| ICH  | International Conference on Harmonisation |
| IRB  | Institutional Review Board                |
| N    | Number (typically refers to subjects)     |
| OHRP | Office for Human Research Protections     |
| PHI  | Protected Health Information              |
| PI   | Principal Investigator                    |
| QA   | Quality Assurance                         |
| QC   | Quality Control                           |
| SOP  | Standard Operating Procedure              |
| UP   | Unanticipated Problem                     |

## PROTOCOL SUMMARY

**Title:** A Pilot Prospective, Randomized Controlled Trial Assessing the Clinical Impact of Integrated Pharmacogenetic Testing on Selected OASIS Metrics, Re-hospitalizations and Emergency Department visits

**Synopsis:** Patients meeting eligibility criteria will be randomized into two groups, one receiving pharmacogenetic testing and the other not receiving pharmacogenetic testing. In this open-label trial, a pharmacist will make medication therapy recommendations using YouScript® Personalized Prescribing System for patients who receive genetic testing and standard drug information resources per usual for patients who do not undergo pharmacogenetic testing.

Both groups will be followed for 60 days. The number of re-hospitalizations and emergency department (ED) visits will be recorded as well as time to first re-hospitalization and time to first ED visit. Select OASIS metrics (e.g. M1034, M1242, M1710, M1720, M1745, M2110) and depression using PHQ-2 will be evaluated and documented at time of admission to home health, at 30 days, and at 60 days for improvement in overall status, pain, confusion, anxiety, depression, disruptive behavior, and the need for assistance with activities of daily living (ADLs) and instrumental activities of daily living (IADLs). The number of falls will be collected as well as the proportion of YouScript® recommendations accepted by study pharmacist and passed on to clinicians and the proportion of recommendations accepted by clinicians.

**Objectives:**

Primary:

- To assess the number of re-hospitalizations at 30 and 60 days post discharge with pharmacogenetic testing and YouScript® Personalized Prescribing System
- To assess the number of Emergency Department visits at 30 and 60 days post discharge with pharmacogenetic testing and YouScript® Personalized Prescribing system

Exploratory:

- To assess time to first re-hospitalization.
- To assess time to first Emergency Department visit.
- To assess the impact of genetic testing on overall status according to OASIS M1034 at 30 and 60 days post discharge.
- To assess the impact of genetic testing on frequency of pain according to OASIS M1242 at 30 and 60 days post discharge.
- To assess the impact of genetic testing on frequency of confusion according to OASIS M1710 at 30 and 60 days post discharge.
- To assess the impact of genetic testing on frequency of anxiety

according to OASIS M1720 at 30 and 60 days post discharge.

- To assess the impact of genetic testing on depression according to PHQ-2 at 30 and 60 days post discharge.
- To assess the impact of genetic testing on frequency of disruptive behavior according to OASIS M1745 at 30 and 60 days post discharge.
- To assess the impact of genetic testing on the frequency of ADL and IADL assistance according to OASIS M2110 at 30 and 60 days post discharge.
- To assess whether YouScript® testing decreases falls
- To assess the proportion of YouScript® Personalized Prescribing System recommendations accepted by the study pharmacist and passed on to clinicians.
- To assess the proportion of study pharmacist recommendations acted on by clinicians.

**Sample size** 100 patients (50 intervention, 50 controls)

**Population:** The study population consists of patients aged 65 and older who are currently enrolled in home health and are presently taking or initiating treatment with at least one oral form of medication with a significant drug-drug or drug-gene interaction as defined by FDA boxed warning, FDA cautionary labeling, clinical literature or a YouScript® algorithm-predicted significant effect.

Those meeting eligibility criteria will be prospectively enrolled in either the “tested” group and undergo YouScript® testing or “untested” group and not undergo YouScript® testing.

**Description of Intervention:** Patients in the “tested” group will receive genetic testing. The study pharmacist will review drug-drug, drug-gene, and drug-drug-gene interactions using YouScript® Personalized Prescribing System to provide drug therapy recommendations to prescribers.

**Estimated Time to Complete Enrollment:** Up to 20 weeks (5+ months)

**Subject Participation Duration:** Each patient will be followed for 60 days from date of admission to home health

**Total Study Duration:** Up to 8 months, depending on the rate of accrual

**Figure 1:** Schematic of Study Design.

[figure not shown]

# 1 BACKGROUND & RATIONALE

## 1.1 Overview

Drug-drug interactions (DDIs) are widely recognized as a major cause of adverse drug reactions. Numerous drug databases are available for pharmacists and clinicians to check for potential DDIs. More recently discovered and vitally important are drug-gene interactions (DGIs) and drug-drug-gene interactions (DDGIs). Cytochrome P-450 enzymes reduce or alter the pharmacologic activity of many drugs and facilitate their elimination. Additionally, genetic variance among patients who are abnormal metabolizers compounds the potential risk for adverse effects and often results in decreased efficacy. Variance in drug levels presents a major therapeutic problem in dosage optimization.

At this point, clinicians can only determine potential DDIs but not DGIs and DDGIs. Knowledge of genetic variations in metabolism within a patient can potentially circumvent adverse effects and allow proper dosage adjustments. YouScript® Personalized Prescribing System, by including a patient's genetic profile, uses an algorithm to flag actual and potential DDIs, DGIs, and DDGIs, provides a list of safer alternatives, contains package inserts for medications, and has direct links to evidence-based literature to support recommendations. Having access to such a database can allow for "personalized prescribing" resulting in decreased hospitalizations, medication-related adverse effects, and emergency department visits while increasing patient efficacy and quality of life and improving clinical-decision making.

### 1.1.1 Home health patients

The majority of patients receiving home health care are aged 65 and older, take multiple medications, and have poor compliance due to adverse drug effects, which often times leads to emergency department visits, hospitalizations, and decreased quality of life. Knowledge of a patient's genetic profile will allow clinicians to make medication therapy decisions specific to each patient leading to better outcomes such as decreased pill burden, improvement of disease state, decreased adverse drug reactions, and increased quality of life. Better outcomes will reduce medical costs for both patients and healthcare systems.

### 1.1.2 Medication-Related Problems

Medication-Related Problems (MRPs) are common among people who take multiple medications. MRPs often result in Adverse Drug Reactions (ADRs) or a therapeutic failure. A medication-related problem (MRP) is as an event or circumstance involving drug treatment that actually or potentially interferes with the patient experiencing an optimum outcome of medical care. Classifications of MRPs include poor compliance, adverse drug reactions, drug interactions, unnecessary drug therapy, additional medication therapy need, and dosage too high/low, etc. Patients are harmed by MRPs. For example, routinely prescribed psychiatric medications are a common cause of adverse drug reaction

---

 Wilkinson GR. Drug Metabolism and Variability among Patients in Drug Response. NEJM 2005; 352(21): 2211-21.

driven emergency room visits. Emergency room visits and hospitalizations associated with drug therapy problems undoubtedly increase healthcare system costs.

### **1.1.3 OASIS metrics**

The Centers for Medicare and Medicaid Services (CMS) requires that Home Health Agencies (HHAs) report data from the Outcome and Assessment Information Set (OASIS) as a condition of participation from HHAs. OASIS data is used to define the quality of HHAs and need for improvement. OASIS data helps measure the rates for use of specific evidenced-based care processes in order to promote best practices across the home health industry.

### **1.1.4 Polypharmacy among home health patients**

Home health patients are typically prescribed multiple medications. Further, older adults are at a higher risk of emergency hospitalizations due to adverse drug reactions. This has major consequences. For example, the national average for percent of long-stay nursing home residents experiencing one or more falls with major injury is 3.2%. On average, the hospitalization cost for a fall injury is \$34,294 (in 2012 dollars).

### **1.1.5 Benefits of pharmacogenetic testing**

Pharmacogenetic testing is a new, evolving area of research and has the potential to predict and reduce unnecessary medication related adverse events. Drug and gene interactions cause approximately 34% of significant interaction warnings that can lead to side effects. This study will provide insight into the clinical utility of these tests. The value of pharmacogenetic testing to optimize patient outcomes has been demonstrated in psychiatry.

Ideally, in addition to considering a polypharmacy patient's existing burden of medications, a clinician would be able to also consider the patient's genetics. To factor in all of the information, however, is challenging. Sophisticated software is increasingly able to calculate the multitude of data points pertaining to medications and genetics. In order to do so, clinicians would need to obtain genetic testing and utilize software to generate

---

 L Hampton, et al, Emergency Department Visits by Adults for Psychiatric Medication Adverse Events, Journal of the American Medical Association: Psychiatry, July 2014.

 Acumen, LLC, Medication Therapy Management in Chronically Ill Populations: Final Report, [http://innovation.cms.gov/Files/reports/MTM\\_Final\\_Report.pdf](http://innovation.cms.gov/Files/reports/MTM_Final_Report.pdf)

 [http://www.cms.gov/Medicare/Quality-Initiatives-Patient-Assessment-Instruments/OASIS/index.html?redirect=/oasis/01\\_overview.asp](http://www.cms.gov/Medicare/Quality-Initiatives-Patient-Assessment-Instruments/OASIS/index.html?redirect=/oasis/01_overview.asp)

 D Budnitz, et al, Emergency Hospitalizations for Adverse Drug Events in Older Americans, The New England Journal of Medicine, v365, n21, November 2011.

 J Fagerness, et al, Pharmacogenetic-Guided Psychiatric Intervention Associated With Increased Adherence and Cost Savings, American Journal of Managed Care, v20, n5, May 2014.

recommendations regarding care. Currently the testing is used sporadically, typically unaccompanied by software analysis. To effect this change, data is needed to support the utility of the testing. The proposed study must be conducted in order to obtain the necessary data.

Pharmacogenetic testing, in combination with drug and gene interaction risk analysis software such as the YouScript® Personalized Prescribing System, can help identify the following MRPs: Improper drug selection, sub-therapeutic dosage, overdose, drug interactions, and adverse drug reactions.

#### **1.1.6 YouScript Personalized Prescribing System**

Genelex Corporation is a leader in comprehensive medication management based on the YouScript® clinical decision support tool and DNA drug sensitivity testing. The purpose of the YouScript® personalized prescribing system is to improve patient outcomes by decreasing the risk of adverse drug reactions (ADRs) and therapeutic failures caused by drug-drug, drug-gene and drug-drug-gene interactions. ADRs prevented by the YouScript® system include overdose toxicity and treatment failure caused by individual variation in pharmacokinetics caused by patient drug regimens and genetics. The YouScript® system synthesizes decades of publicly funded basic and clinical research to provide actionable information to clinicians treating patients taking multiple medications.

Controlling prescription drug treatment risk is complex because more than 85% of patients have significant genetic variation in the cytochrome p450 genes that metabolize the majority of the most commonly prescribed medications. Genetic variability in a patient's ability to metabolize many drugs can increase the risk of an ADR and impact treatment effectiveness. Drug-related problems (DRPs) are a major healthcare burden with an estimated cost of \$289 billion per year in added health care costs. Elderly patients, in particular, are at greater risk of an ADR^11, as they are often on multiple medications. Two-thirds of adults over age 65 use one or more prescription drugs daily. Patients aged 60 years and older account for 51% of the deaths from ADRs. Although this age group represents about 17% of the U.S. population, it accounts for 39% of hospitalizations. Ten to 17% of hospitalizations of older patients are directly related to ADRs. Upon discharge, 50% of patients with ADRs experienced

---

 Thinking Outside the Pillbox: A System-wide Approach to Improving Patient Medication Adherence for Chronic Disease A NEHI Research Brief – August 2009 ([http://www.nehi.net/writable/publication\\_files/file/pa\\_issue\\_brief\\_final.pdf](http://www.nehi.net/writable/publication_files/file/pa_issue_brief_final.pdf))

## 1.2 Rationale

It is not known whether referrals for YouScript® testing, which can identify MRPs, in fact prevents ADRs or otherwise reduces risk of harm among home health patients. The researchers seek to determine whether they could detect improvements in medication-related Medicare quality measures before and after initiating the YouScript® Personalized Prescribing System in home health care patients at high risk of genetically based adverse drug events.

## 1.3 Hypotheses

The investigator hypothesizes that patients who undergo testing via the YouScript® Personalized Prescribing System, relative to those who do not get testing, will return the hospital and emergency department less often.

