# 2 STUDY DESIGN & OBJECTIVES

The open-label study is designed as a pilot prospective, randomized controlled trial to assess the impact of the YouScript® Personalized Prescribing System on decreased re-hospitalizations, ED visits, falls, and improvement in select OASIS metrics and clinical decision-making. The decision to utilize the YouScript® Personalized Prescribing System and all treatment decisions will be made in accordance with usual care practice, and will be made prior to the decision to participate in the study.

Outcomes will be compared between a group of prospectively enrolled patients undergoing CYP2D6, CYP2C19, CYP2C9, VKORC1, CYP3A4, and CYP3A5 testing with the YouScript® Personalized Prescribing System at the discretion of their clinician (i.e. “tested” patients) and a group of similar patients at home health meeting the same enrollment criteria (excluding the YouScript® testing) and matched on key characteristics to the tested patients using propensity score matching.

The study aims to initially enroll 100 patients from a single home health agency in the United States. The study includes 2 study arms.

| Arm | Sample size | Treatment | Treatment |
|-----|-------------|-----------|-----------|
|-----|-------------|-----------|-----------|

|              |    |            |                                                               |
|--------------|----|------------|---------------------------------------------------------------|
| Intervention | 50 | Tested     | YouScript®                                                    |
| Controls     | 50 | Not tested | Treatment as usual (i.e. standard drug information resources) |

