#### **3.3.2 Enrollment/Baseline**

Any new data will be collected during regularly scheduled nursing visits. Principal investigator will review to verify that subjects continue to meet the eligibility criteria.

- Obtain and document consent from subject on study consent form
- Verify inclusion/exclusion criteria
- Obtain demographic information, medical history, medication history, alcohol, and tobacco use history
- Collect blood/urine/saliva/other specimen
- Record results of selected OASIS metrics and PHQ-2
- For those randomized to intervention:
  - Collect buccal swab for testing

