### **3.4 Randomization Procedures**

Prior to enrollment the treatment assignments were generated as a simple random sample, with 50 patients in each treatment arm. The randomization was carried out in R version 3.1.1 (Vienna, Austria).

Patients will be numbered chronologically by date of enrollment and each number has been randomized *a priori* to a treatment arm as stated above. Nurses are assigned patients based on coverage area and schedule. Only the PI will have access to the randomization list as to avoid any manipulation of patients to different treatment arms.

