## **7 STATISTICAL CONSIDERATIONS**

The statistical analysis will include the comparison of the YouScript® and control groups the primary and exploratory outcomes. Poisson regression will be used to compare the number of re-hospitalizations at 30 days, the number of re-hospitalizations at 60 days, the number of ED visits at 30 days, the number of ED visits at 60 days and the number of falls. The log-rank test will be used to compare the time to the first re-hospitalization and the time to the first ER visit. OASIS and PHQ-2 scores will be compared using the Wilcoxon rank sum test. The chi-squared test or the Fisher's exact test (as needed) will be used to compare the proportion of cases with acceptance by the study pharmacist and passing on to clinicians and the proportions of recommendations acted on by clinicians. Calculations will be carried out in R (Vienna, Austria). All tests will be two-sided.  $P < 0.05$  will be used to denote statistical significance. As the study is designed as a pilot, tests will not be adjusted for multiple comparisons.

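### The protocol compares patients by testing received in some sections and by randomised arm in others, and the statistical section does not say which applies

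*Combined protocol and SAP*

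**What the plan says.** Two places describe the contrast by receipt of testing. Section 1.3 states the hypothesis for "patients who undergo testing via the YouScript® Personalized Prescribing System, relative to those who do not get testing". Section 2 goes further, because it describes the comparison of outcomes itself: "Outcomes will be compared between a group of prospectively enrolled patients undergoing CYP2D6, CYP2C19, CYP2C9, VKORC1, CYP3A4, and CYP3A5 testing". The same sentence leaves testing to the clinician's discretion and takes as comparator a group of untested patients "matched on key characteristics to the tested patients using propensity score matching".

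Three places form the groups by randomisation. The Protocol Summary says "Patients meeting eligibility criteria will be randomized into two groups, one receiving pharmacogenetic testing and the other not receiving pharmacogenetic testing". Section 3.4 says "the treatment assignments were generated as a simple random sample, with 50 patients in each treatment arm". Section 3.3.2 lists the buccal swab under the words "For those randomized to intervention", so assignment comes before the swab.

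Section 7 says "The statistical analysis will include the comparison of the YouScript® and control groups" and names the model for the primary outcomes: "Poisson regression will be used to compare the number of re-hospitalizations at 30 days", and likewise for the other counts. It does not say whether a patient belongs to a group by assignment or by testing. The separate statistical analysis plan section repeats this text. The amendments of March 24, 2016 add outcomes, drop two comparisons and bring in negative binomial regression, but define no analysis population. No intention-to-treat, per-protocol or other analysis set is defined anywhere.

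Section 3.6 lets patients withdraw, lets the investigator end a patient's participation, and enrols replacements. It does not say whether data from withdrawn patients stay in the analysis.

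**The concern.** A randomised comparison is protected only while patients are analysed in the arm they were assigned. If Section 2 were followed as written, a patient assigned to testing who had no swab or no result would be either left out or counted as untested, and a control tested outside the study might move the other way. Removal of withdrawn patients from the data could have a similar effect.

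If the patients who leave a group differ in risk from those who stay, the rate ratio moves away from its true value even when testing does nothing. The trial is open-label, and the principal investigator both holds the randomization list (Section 3.4) and enters the outcome data (Section 5.1). An unwritten rule on who is counted where is therefore hard for a reader to accept on trust.

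**Working it through.** **Step 1. What can be reproduced.** The documents give 50 + 50 = 100 patients. They give no event rate, effect size, power, dropout rate or number expected to go untested. The size of any bias therefore cannot be derived, and everything below rests on assumed inputs.

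**Step 2. The sections side by side.**

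| Place | How the groups are described |
|---|---|
| 1.3 Hypotheses | by testing received |
| 2 Study Design & Objectives, comparison sentence | by testing received, at clinician discretion, against matched untested patients |
| Protocol Summary | by randomisation |
| 3.3.2 Enrollment/Baseline | by randomisation, swab afterwards |
| 3.4 Randomization Procedures | by a list fixed in advance, 50 per arm |
| 7 Statistical Considerations | named groups, basis of membership not stated |
| 3.6 Subject Withdrawal | withdrawn patients replaced, use of their data not stated |

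Section 2 is not consistent within itself: it calls the study a randomised controlled trial and tabulates two arms of 50, then describes a matched comparison.

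**Step 3. Illustration A: untested patients each have one early event.** True rate ratio 1. Let m be the mean events per patient in both arms (assumed 0.3 or 0.5) and u the number of the 50 intervention patients not tested (assumed 2 or 5).

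- Dropped: RR = [(50m − u)/(50 − u)] / m
- Moved to control: RR = [(50m − u)/(50 − u)] / [(50m + u)/(50 + u)]

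| m | u | Dropped | Moved to control |
|---|---|---|---|
| 0.5 | 2 | (23/48)/0.5 = 0.96 | (23/48)/(27/52) = 0.92 |
| 0.5 | 5 | (20/45)/0.5 = 0.89 | (20/45)/(30/55) = 0.81 |
| 0.3 | 2 | (13/48)/0.3 = 0.90 | (13/48)/(17/52) = 0.83 |
| 0.3 | 5 | (10/45)/0.3 = 0.74 | (10/45)/(20/55) = 0.61 |

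The last row is severe by construction. It places 5 of the arm's 15 events on untested patients, whose rate of 1.0 is 4.5 times the 10/45 = 0.22 of the tested.

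**Step 4. Illustration B: untested patients have r times the event rate of tested patients.** With f = u/50, the tested rate relative to the arm mean is t = 1/[(1 − f) + f·r]. Dropping the untested gives RR = t. Moving them gives RR = t / [(50 + u·r·t)/(50 + u)].

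| u | r | Dropped | Moved to control |
|---|---|---|---|
| any | 1 | 1.00 | 1.00 |
| 2 | 2 | 0.96 | 0.93 |
| 5 | 2 | 0.91 | 0.85 |
| 5 | 3 | 0.83 | 0.73 |
| 10 | 2 | 0.83 | 0.75 |
| 10 | 3 | 0.71 | 0.60 |

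The direction is not fixed. With u = 5 and r = 0.5, t = 1/(0.9 + 0.05) = 1.05. Moving those patients gives 1.053/[(50 + 2.63)/55] = 1.10, which is against testing.

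**Step 5. Type I error.** This comes from 200,000 simulated trials per setting, with Poisson counts and a two-sided Wald test at 0.05. At an assumed 0.5 events per patient, the as-assigned analysis gives 0.046. With u = 5 and r = 2 it is 0.057 (dropped) or 0.082 (moved). With u = 10 and r = 3 it is 0.156 or 0.368. Over 0.3 to 1.0 events per patient, u of 5 or 10 and r of 2 or 3, the range is 0.048 to 0.293 (dropped) and 0.063 to 0.653 (moved). The simulation assumes no over-dispersion.

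**The case against.** Much can be said on the other side.

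First, a reader might infer from Sections 1.3 and 2 that the plan defines its groups by testing received and not by arm. The documents do not support that as a general statement. The Protocol Summary and Sections 3.3.2 and 3.4 form the groups by randomisation, Section 7 uses names that read like arms, and the 2016 amendments refer to the intervention and the control group. A hypothesis sentence describes the intervention and does not define an analysis set. No section says that an untested intervention patient is dropped or counted as a control. All of this stands, so the finding is a contradiction and an omission.

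Second, a reader might infer that early re-admission or death is a likely reason for going untested, so that the bias must favour testing. The schedule leaves little room for this. Section 3.3.1 lists the swab at screening, Section 3.3.2 at enrolment or baseline, and Appendix A puts testing at Day 0. A patient swabbed then and re-admitted later has undergone testing on any ordinary reading. A failed sample has no stated link to risk, and with no link the rate ratio is 1.00. This also stands, with one limit: the documents do not say whether *tested* requires a reported result, which would come after the swab.

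Third, the illustrations build in their effect through the assumed rates. That is so, and they show only what an as-tested rule could do.

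The objection does not remove two facts. Section 2 states a comparison that conflicts with randomisation, and nothing in Section 7 overrides it. Section 3.6 also gives a documented way for a randomised patient to leave the analysis, which does not depend on when the swab is taken.

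**Conclusion.** The point holds as a contradiction that should be resolved. Sections 1.3 and 2 describe the comparison by testing received, the Protocol Summary and Sections 3.3.2 and 3.4 form the groups by randomisation, and Section 7 does not settle which governs. Section 3.6 leaves the data of withdrawn and replaced patients undefined. An as-tested analysis is permitted, and Section 2 as written describes one.

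Bias needs two things: some assigned patients untested or withdrawn, and an event rate among them that differs from the rest. Neither is given, so the size is unknown and may be zero. The ranges of 0.74 to 0.96 (dropped) and 0.61 to 0.92 (moved) hold only for 2 to 5 of 50 untested, one early event each, and 0.3 to 0.5 events per patient. The documents do not show that any patient was dropped or moved, or that any result is biased.

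**What to change.** In Section 7, state the following:

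- All randomised patients are analysed in the arm on the randomization list, whether or not a swab, a result or a recommendation was obtained.
- Controls tested outside the study stay in the control arm.
- Withdrawn patients stay in their assigned arm with data up to withdrawal, using log follow-up time as an offset in the count models. Replacements are added to the randomised patients and are not substituted for those withdrawn.
- The numbers tested and not tested are reported for each arm, and any as-tested analysis is labelled a sensitivity analysis.

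Reword Sections 1.3 and 2 to *assigned to* testing or no testing. Remove the clinician-discretion and propensity-matching text from Section 2, or reconcile it with the randomised design.

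The 2016 amendments were written after study completion. If the analysis was already done as assigned, a dated statement to that effect is enough. If not, the as-assigned analysis should be run and reported as primary.

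The cost is wording in three sections, a follow-up end date for each withdrawn patient and, if needed, one re-run of the models. The estimate may be less favourable to testing. The analysed number may exceed 100 if withdrawn patients were replaced.
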